### **10.1.4 Data Protection**

Subjects will be assigned a unique identifier by the Sponsor. Any subject records or datasets that are transferred to the Sponsor will contain the identifier only; subject names or any information which would make the subject identifiable will not be transferred.

The subject must be informed that his/her personal study-related data will be used by the Sponsor in accordance with local data protection law. The level of disclosure must also be explained to the subject, who will be required to give consent for their data to be used as described in the informed consent.

The subject must be informed that his/her medical records may be examined by Clinical Quality Assurance auditors or other authorised personnel appointed by the Sponsor, by appropriate IRB/IEC members, and by inspectors from regulatory authorities.

### 10.1.5 Committees Structure (IDMC)

An IDMC will be responsible for closely reviewing the data collected during Part 1 and providing their recommendations in the following situations:

- During enrolment of Cohort 1, Cohort 2 or Cohort 3 (Part 1), if one or both of the 2 sentinel subjects experience a serious adverse reaction or if both sentinel subjects experience Grade  $\geq 3$  treatment-related AEs, enrolment will be suspended pending a review of the data by the IDMC, who will make a recommendation regarding study continuation.
- If at any point during Cohort 1, Cohort 2 or Cohort 3, a serious adverse reaction is reported in 1 or more subjects, or Grade  $\geq 3$  treatment related AEs are reported in 2 or more subjects, enrolment will be suspended pending the outcome of an IDMC review.
- After all 9 subjects are enrolled and treated in Cohort 1 and the last subject has been treated and monitored for 24 hours, if 1 or more of the 9 subjects experience a serious adverse reaction, or if 2 or more of the 9 subjects experience a Grade  $\geq 3$  treatment-related AE, the IDMC will review available data to make a recommendation on starting Cohort 2.
- After all 9 subjects are enrolled and treated in Cohort 2 and the last subject has been treated and monitored for 24 hours, if 1 or more of the 9 subjects experience a serious adverse reaction, or if 2 or more of the 9 subjects experience a Grade  $\geq 3$  treatment-related AE, the IDMC will review available data to make a recommendation on starting Cohort 3.

Due to the recruitment challenge of low hospitalisation rates in the limited number of sites participating in Part 1 of this study, the IDMC will be asked to make a recommendation to progress to Part 2 of this study (with or without modifications to the study design and protocol), based on the interim analysis of the Phase 1a study in healthy subjects, supplemented with the available data from Part 1 of this study, even if not all Part 1 cohorts have reached the planned enrolment.

Further information is provided in the IDMC Charter.

### 10.1.6 Dissemination of Clinical Study Data

When the clinical study report is completed, the Sponsor will provide the major findings of the trial to the Investigator. A summary of the trial results will also be posted in a publicly accessible database (e.g., [www.ClinTrials.gov](http://www.ClinTrials.gov)). The results may also be submitted for publication.

### 10.1.7 Data Quality Assurance

- All subject data relating to the study will be recorded on electronic CRF unless transmitted to the Sponsor or designee electronically (e.g., laboratory data). The Investigator is responsible for verifying that data entries are accurate and correct by physically or electronically signing the CRF.
- The Investigator must maintain accurate documentation (source data) that supports the information entered in the CRF.
- The Investigator must permit study-related monitoring, audits, IRB/IEC review, and regulatory agency inspections and provide direct access to source data documents.
- Monitoring details describing strategies (e.g., risk-based initiatives in operations and quality such as Risk Management and Mitigation Strategies and Analytical Risk-Based Monitoring), methods, responsibilities, and requirements, including handling of noncompliance issues and monitoring techniques (central, remote, or on-site monitoring) are provided in the Monitoring Plan and Risk Management Plan.
- The Sponsor or designee is responsible for the data management of this study, including quality checking of the data.
- The Sponsor assumes accountability for actions delegated to other individuals (e.g., Contract Research Organisations).
- Study monitors will perform ongoing source data verification to confirm that data entered into the CRF by authorised site personnel are accurate, complete, and verifiable from source documents; that the safety and rights of subjects are being protected; and that the study is being conducted in accordance with the currently approved protocol and any other study agreements, ICH GCP, and all applicable regulatory requirements.
- Records and documents, including signed ICF, pertaining to the conduct of this study must be retained by the Investigator for at least 2 years after the last approval of a marketing application or 15 years from completion of the study (whichever is longer), unless local regulations or institutional policies require a longer retention period. No records may be destroyed during the retention period without the written approval of the Sponsor. No records may be transferred to another location or party without written notification to the Sponsor.
- All data generated by the site personnel will be captured electronically at each study site using eCRFs. Data from external sources (such as laboratory data) will be imported into the database. Once the eCRF clinical data have been submitted to the central server at the independent data centre, corrections to the data fields will be captured in an audit trail. The reason for change, the name of the person who performed the change, together with the time and date will be logged to provide an audit trail.

- If additional corrections are needed, the responsible monitor or data manager will raise a query in the EDC application. The appropriate staff at the study site will answer queries sent to the Investigator. The name of the staff member responding to the query, and time and date stamp will be captured to provide an audit trail. Once all source data verification is complete, and all queries are closed, the monitor will freeze the eCRF page.
- The specific procedures to be used for data entry and query resolution using the EDC system/eCRF will be provided to study sites in a training manual. In addition, site personnel will receive training on the EDC system/eCRF.

### **10.1.8 Source Documents**

Source documents provide evidence for the existence of the subject and substantiate the integrity of the data collected. Source documents are filed at the Investigator's site.

Data reported on the CRF or entered in the eCRF that are transcribed from source documents must be consistent with the source documents, or the discrepancies must be explained. The Investigator may need to request previous medical records or transfer records, depending on the study. Also, current medical records must be available.

### **10.1.9 Study and Site Start and Closure**

The study start date is the date on which the clinical study will be open for the recruitment of subjects.

The first act of recruitment is the first subject signing consent.

The Sponsor designee reserves the right to close the study site or terminate the study at any time for any reason at the sole discretion of the Sponsor. Study sites will be closed upon study completion. A study site is considered closed when all required documents and study supplies have been collected and a study site closure visit has been performed.

The Investigator may initiate study site closure at any time, provided there is reasonable cause and sufficient notice is given in advance of the intended termination.

Reasons for the early closure of a study site by the Sponsor or Investigator may include but are not limited to:

- Failure of the Investigator to comply with the protocol, the requirements of the IRB/IEC or local health authorities, the Sponsor's procedures, or GCP guidelines
- Inadequate recruitment of subjects by the Investigator

- Discontinuation of further study treatment development

If the study is prematurely terminated or suspended, the Sponsor shall promptly inform the Investigators, the IECs/IRBs, the regulatory authorities, and any contract research organisation(s) (CRO) used in the study of the reason for termination or suspension, as specified by the applicable regulatory requirements. The Investigator shall promptly inform the subject and should assure appropriate subject therapy and/or follow-up.

#### **10.1.10 Publication Policy**

- The results of this study will be published by the Sponsor in collaboration with Investigators.
- Investigators may publish or present other subject data or case reports at scientific meetings. If this is foreseen, the Investigator agrees to submit all manuscripts or abstracts to the Sponsor before submission. This allows the Sponsor to protect proprietary information and to provide comments.
- The Sponsor will comply with the requirements for publication of study results. In accordance with standard editorial and ethical practice, the Sponsor will generally support publication of multicentre studies only in their entirety and not as individual site data. In this case, a coordinating Investigator will be designated by mutual agreement.
- Authorship will be determined by mutual agreement and in line with International Committee of Medical Journal Editors authorship requirements.

#### **10.1.11 Protocol Approval and Amendment**

Before the start of the study, the study protocol and/or other relevant documents will be approved by the IEC/IRB/Competent Authorities, in accordance with local legal requirements. The Sponsor must ensure that all ethical and legal requirements have been met before the first subject is enrolled in the study.

This protocol is to be followed exactly. To alter the protocol, amendments must be written, receive approval from the appropriate personnel, and receive IRB/IEC/Competent Authority approval prior to implementation (if appropriate). In the US: Following approval, the protocol amendment(s) will be submitted to the IND under which the study is being conducted.

Administrative changes (not affecting the subject benefit/risk ratio) may be made without the need for a formal amendment. All amendments will be distributed to all protocol recipients, with appropriate instructions.

### **10.1.12 Liability and Insurance**

The Sponsor will take out reasonable third-party liability insurance cover in accordance with all legal requirements. The civil liability of the Investigator, the persons instructed by him or her and the hospital, practice, or institute in which they are employed, and the liability of the Sponsor with respect to financial loss due to personal injury and other damage that may arise as a result of the carrying out of this study are governed by the applicable law.

The Sponsor will arrange for subjects participating in this study to be insured against financial loss due to personal injury caused by the pharmaceutical products being tested or by medical steps taken in the course of the study.

#### **10.1.12.1 Access to Source Data**

During the study, a monitor will make site visits to review protocol compliance, compare eCRF entries and individual subject's medical records, assess drug accountability, and ensure that the study is being conducted according to pertinent regulatory requirements. The eCRF entries will be verified with source documentation. The review of medical records will be performed in a manner to ensure that subject confidentiality is maintained.

Checking of the eCRF entries for completeness and clarity, and cross-checking with source documents, will be required to monitor the progress of the study. Moreover, regulatory authorities of certain countries, IRBs, IECs, and/or the Sponsor's Clinical Quality Assurance Group may wish to carry out such source data checks and/or on-site audit inspections. Direct access to source data will be required for these inspections and audits; they will be carried out giving due consideration to data protection and medical confidentiality. The Investigator assures Parexel and the Sponsor of the necessary support at all times.

## 10.2 Appendix 2: 8-Point Ordinal Scale

The worst clinical status (i.e., the highest ordinal scale) of the day will be recorded.

| Score | Description                                                                                                                                                       |
|-------|-------------------------------------------------------------------------------------------------------------------------------------------------------------------|
| 1     | Not hospitalised, no limitations of activities                                                                                                                    |
| 2     | Not hospitalised, limitation of activities, home oxygen requirement, or both                                                                                      |
| 3     | Hospitalised, not requiring supplemental oxygen and no longer requiring ongoing medical care (used if hospitalisation was extended for infection-control reasons) |
| 4     | Hospitalised, not requiring supplemental oxygen but requiring ongoing medical care (SARS-CoV-2 – related or other medical conditions)                             |
| 5     | Hospitalised, requiring any supplemental oxygen                                                                                                                   |
| 6     | Hospitalised, requiring non-invasive ventilation or use of high-flow oxygen devices                                                                               |
| 7     | Hospitalised, receiving invasive mechanical ventilation or ECMO                                                                                                   |
| 8     | Death                                                                                                                                                             |

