| Efficacy                                                                                                                  |                        |                           |                                                                           |                |                |              |               |                |                |              |              |                |                 |
| Clinical status (8-point ordinal scale)                                                                                   |                        | X (pre-dose)              | Daily until hospital discharge and at each visit after hospital discharge |                |                |              |               |                |                |              |              |                |                 |
| Respiratory parameters b                                                                                       |                        | X (pre-dose)              | X                                                                         | X              | X              | X            | X             | X              | X              | X            | X            | X              | X               |
| COVID-19-Related Symptoms h                                                                                    |                        | X (pre-dose)              | X                                                                         | X              | X              | X            | X             | X              | X              | X            | X            | X              | X               |

|                                    | Screening a | Treatment period                  | Endpoint Assessment period |             |                |                |                |               |                | Extended FU    |                | Discharge | ED             |
|------------------------------------|------------------------|-----------------------------------|----------------------------|-------------|----------------|----------------|----------------|---------------|----------------|----------------|----------------|-----------|----------------|

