## **8.1 Efficacy Assessments**

### **8.1.1 Clinical Status According to 8-point Ordinal Scale**

The clinical status will be assessed at the timepoints specified in the SoA (Table 1-1 for Part 1 and Table 1-2 for Part 2), using an 8-point ordinal scale (see Appendix 2), previously used in Study NCT04280705 (Beigel et al 2020).

Recovery will be defined as achieving a clinical status  $\leq 3$  on the 8-point ordinal scale. This will be considered 'sustained recovery' if the clinical status remains  $\leq 3$  for the subsequent 14 consecutive days. Time to sustained recovery will be defined as the time between treatment administration and the first occurrence of recovery which is subsequently shown to be sustained..

Deterioration in the clinical condition of the subject such that intensive care is required will be considered a treatment failure and the end of study visit should be performed.

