## 9 Statistical Considerations

### 9.1 Statistical Hypotheses

**Part 1:** No formal hypothesis is postulated for Part 1.

**Part 2:** In Part 2, capacity of XVR011 in reducing time to recovery (sustained) as compared to placebo will be tested in a superiority setting. The primary endpoint will be tested using the stratified log-rank test. It is assumed that the placebo and active cumulative survival curves for TTR do not follow an exponential distribution. Moreover, the HR cannot be assumed as constant during the 28-day FU period.

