### 9.2 Sample Size Determination

**Part 1:** There is no formal sample size calculation for Part 1. Considering the target of XVR011 is a viral protein and the absence of any binding with human proteins in preclinical studies, 9 subjects per cohort are considered adequate as an initial assessment of the safety of a single dose of XVR011 in this population.

**Part 2:** The sample size for the Phase 2 part of the study is based on the primary endpoint, time to recovery defined as reaching level 1 to 3 of the 8-point scale within 28-day FU period and which is maintained at or below level 3 for the subsequent, consecutive 14 days; a 2:1 randomisation with a one-sided alpha of 0.025, 80% power and allowing for a 15% drop-out rate. The sample size required to test the primary endpoint is obtained by comparing with the log-rank test, the piecewise exponential cumulative survivals described in Table 9–1 and is 408 subjects allowing 275 events to be observed. A total of 408 subjects will be randomised, 272 to the XVR011 arm and 136 to the placebo arm.

**Table 9–1**                      **Determination of Sample Size with Different Time to Recovery Assumptions for Placebo and XVR011 Treatment**

|               | Placebo Cumulative
“Survival”* | XVR011 Cumulative
“Survival”* | HR   |
|---------------|-----------------------------------|----------------------------------|------|
| Day 1  | 100%                              | 100%                             |      |
| Day 5  | 80%                               | 50%                              | 3.11 |
| Day 7  | 50%                               | 25%                              | 1.47 |
| Day 29 | 20%                               | 20%                              | 0.24 |

\* “Survival” refers to absence of recovery

Note: Sample size scenarios: Primary endpoint time to recovery, 2:1 randomisation, 1-sided alpha = 0.025 and power 80%.

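### Worst-of-day scoring combined with visit-only scoring after discharge can date a Part 2 recovery up to a week late and costs the primary test power

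*Protocol*

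**What the plan says.** Section 8.1.1 of the protocol assesses clinical status at the schedule's timepoints, defines recovery as a status of 3 or lower, and dates it to "the first occurrence of recovery which is subsequently shown to be sustained". Appendix 2 adds the daily recording rule: "The worst clinical status (i.e., the highest ordinal scale) of the day will be recorded". Levels 1 and 2 both require that the subject is not in hospital. Level 3 is the only in-hospital level that counts as recovery, and Appendix 2 annotates it "used if hospitalisation was extended for infection-control reasons". Inclusion criterion 5 requires level 4 or 5 at entry.

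In Part 2 the score is taken "Daily until hospital discharge and at each visit after hospital discharge" (Table 1–2). Under Sections 4.1 and 6.7, visits are daily to Day 4 and then on Days 8, 15, 22 and 29. Neither section says that the discharge date itself counts as the recovery date, and nor does any other part of the protocol.

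Section 9.2 sizes Part 2 with "a 2:1 randomisation with a one-sided alpha of 0.025, 80% power and allowing for a 15% drop-out rate". The sample size is "obtained by comparing with the log-rank test, the piecewise exponential cumulative survivals" of Table 9–1 and "is 408 subjects allowing 275 events to be observed". On the test, Section 9.1 says: "The primary endpoint will be tested using the stratified log-rank test".

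**The concern.** On the day of discharge the worst status is an in-hospital one, so levels 1 and 2 are not available. A subject who needed oxygen or care until going home scores 4 or 5 that day. The next score comes at the next scheduled visit. The Discharge visit does not help, because it falls on the discharge day.

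The gap matters because of where the plan puts its effect. Table 9–1 places the treatment difference at Day 5 and Day 7, and after discharge there is no score between Day 4 and Day 8. Recoveries in that interval are tied at Day 8.

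The date may also differ between sites. Section 4.2 describes level 3 as free of oxygen and of ongoing care for COVID-19. Appendix 2 ties level 3 to infection-control stays, and its level 4 includes care for other medical conditions. Two sites could score the same discharge day 3 and 4, and so date the same recovery up to a week apart.

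**Working it through.** **Inputs.** From Section 9.2 and Table 9–1: one-sided alpha 0.025, 2:1 allocation, 408 randomised (272 + 136), 15% dropout. The share not recovered, placebo / XVR011, is 80% / 50% at Day 5, 50% / 25% at Day 7 and 20% / 20% at Day 29. Visit days come from Table 1–2.

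**1. Reproduce the plan.** The piecewise hazard ratio is the ratio of log survival changes in each interval:
- Days 1–5: ln(0.50)/ln(0.80) = 3.11
- Days 5–7: ln(0.25/0.50)/ln(0.50/0.80) = 1.47
- Days 7–29: ln(0.20/0.25)/ln(0.20/0.50) = 0.24

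These match the printed values. Evaluable subjects: 408 × 0.85 = 347 (231 + 116). Events: 408 × 0.85 × 0.80 = 277, against 275 stated. Simulated log-rank power with recovery dated to the day is 0.81–0.82 at 347. Day dating needs 339 evaluable for 80% power, and 339/0.85 = 399, against 408 stated. The plan's figure is therefore reproduced when recovery is dated to the day.

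**2. Date a direct discharge by the text.** The recorded day is the first scheduled visit after the discharge day.

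| Discharge day | First possible score of 3 or lower | Delay (days) |
|---|---|---|
| 2 or 3 | 3 or 4 | 1 |
| 4 to 7 | 8 | 4 to 1 |
| 8 to 14 | 15 | 7 to 1 |

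**3. Power under Table 9–1.** The share scored level 3 in hospital is an assumption, because the protocol gives none. True times are rounded up or down to a calendar day. Cells show day-dated, then visit-dated power.

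| Analysis | Rounding | 0% level 3 | 50% level 3 |
|---|---|---|---|
| 347 evaluable | up | 0.809 → 0.667 | 0.820 → 0.720 |
| 347 evaluable | down | 0.817 → 0.771 | 0.810 → 0.752 |
| 408, dropout censored | up | 0.911 → 0.815 | 0.901 → 0.826 |
| 408, dropout censored | down | 0.908 → 0.882 | 0.905 → 0.862 |

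With 75% scored level 3, visit-dated power is 0.755–0.773 at 347 and 0.865–0.886 at 408. Including repeat runs, day-dated power is about 0.79–0.82 at 347 and 0.89–0.91 at 408. Visit-dated power, with all or half direct discharges, is about 0.67–0.77 and 0.80–0.88.

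**4. Medians.** If every recovery is a direct discharge, the medians of Day 5 (XVR011) and Day 7 (placebo) both become Day 8. The placebo share unrecovered at Day 8 is then 0.479–0.500, so in a single trial its median can also land on Day 15. The XVR011 share is 0.247–0.249, so a gap of about 23 to 25 points remains at Day 8.

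**5. Type I error.** With both arms drawn from the placebo curve, visit dating rejects in 0.024–0.025 of trials.

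Not modelled: stratification (strata sizes are not given), deaths, the 14-day confirmation and visit windows.

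**The case against.** The strongest reply is that the endpoint is achieving or reaching level 3 or lower, and is nowhere defined as the first recorded score. A discharged subject meets level 1 or 2 by the day after discharge. Fourteen consecutive days cannot be confirmed from weekly scores alone, so status between visits must be inferred anyway, and the statistical analysis plan, not shown here, may say how. This stands in part: the protocol does not forbid dating from discharge. But Section 8.1.1 ties the assessment to the schedule, and following the scoring rule and schedule literally gives the later date.

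Second, the worst-of-day rule alone costs nothing. Moving every recovery to the next day leaves the ranks unchanged, and simulated power is 0.78–0.83. This is correct. The loss needs both the rule and the visit-only scoring.

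Third, a reader might infer that most recoveries are dated late. The documents do not support that, because the share reaching level 3 in hospital is unknown and Section 4.2 words that level broadly.

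Fourth, a reader might infer that the rule removes the planned difference. It does not: discharges on Days 2 and 3 are only one day late, and a clear gap remains at Day 8.

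Fifth, the full analysis set is all randomised subjects. With dropout treated as censoring, power stays near or above 80%.

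**Conclusion.** The point holds as a defect in how the recovery date is fixed. Direct discharges from level 4 or 5 are dated one to seven days late, while level 3 recoveries are dated to the day, and the two descriptions of level 3 leave that distinction partly to the site. If all or half of recoveries are direct discharges, power falls by about 4 to 14 points at 347 evaluable subjects and by about 3 to 10 points at 408 with censoring. In the second setting the loss uses up reserve and does not clearly breach 80%, so a claim that the trial is underpowered goes too far. Nor is there support for a claim of bias towards XVR011: the rule is the same in both blinded arms and Type I error holds. The sizes rest on the Table 9–1 curves, nominal visit days and an assumed share of direct discharges. The plan should be corrected on this point, but the flaw does not invalidate the trial.

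**What to change.** In Section 8.1.1 and Appendix 2, state that:
- for scoring the endpoint, a subject discharged alive counts as level 1 or 2 from the discharge date, and the worst-of-day rule does not apply to that day;
- recovery by discharge is dated to the recorded discharge date and not to the first visit afterwards, subject to the 14-day sustained requirement.

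Use one wording for level 3 in Section 4.2 and Appendix 2.

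The cost is a few sentences in the protocol, a CRF completion note and one derivation line. The discharge date is already needed for the secondary endpoint of time to sustained hospital discharge, so no visits, subjects or data are added. Regaining 80% power under visit dating by enlarging the trial would instead take about 380–390 evaluable subjects (times rounded down) or up to about 460–470 (rounded up). The change should be made before Part 2 scores accrue under different site readings.
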